## Abstract

The prevention of child abuse and neglect is a global public health priority due to its serious, long-lasting effects on personal, social, and economic outcomes. The Children At Risk Model (ChARM) is a wraparound-inspired intervention that coordinates evidence-based parenting- and home-visiting programmes, along with community-based supports, in order to address the multiple and complex needs of families at risk of child abuse or neglect. This paper presents the protocol for a study that will be carried out to evaluate this new service model (i.e. no results available as yet). The study comprises a multi-centre, randomised controlled trial, with embedded economic and process evaluations. The study will be conducted in two child-welfare agencies within socially disadvantaged settings in Ireland. Families with children aged 3-11 years who are at risk of maltreatment (n = 50) will be randomised to either the 20-week ChARM programme (n = 25) or to standard care (n = 25) using a 1:1 allocation ratio. The primary outcomes are incidences of child maltreatment and child behaviour and wellbeing. Secondary outcomes include quality of parent-child relationships, parental stress, mental health, substance use, recorded incidences of substantiated abuse, and out-of-home placements. Assessments will take place at pre-intervention, and at 6- and 12-month follow-up periods. The study is the first evaluation of a wraparound-inspired intervention, incorporating evidence-based programmes, designed to prevent child abuse and neglect within high risk families where children are still living in the home. The findings will offer a unique contribution to the development, implementation and evaluation of effective interventions in the prevention of child abuse and neglect.

The trial is registered with the International Standard Randomised Controlled Trial Number Register (DOI 10.1186/ISRCTN13644600, Date of registration: 3
^rd^ June 2015).

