### Data analysis

***RCT.*** Changes in continuous primary and secondary outcomes at baseline and at six-month follow-up will be compared for the intervention and control groups using ANCOVA, controlling for intervention status, site, baseline score and any other baseline differences identified. Mean difference effect sizes, 95% confidence intervals (CIs), and p values will be reported for continuous outcomes. Changes at 12-month follow up will be conducted using ANOVA. Changes between study arms in categorical variables (i.e. data records of incidences of CM and out-of-home placements) at baseline and six-month follow up will be analysed using the Chi Square test of independence, reporting relative risk, 95% CIs and p values. Descriptive statistical summaries (e.g. means, standard deviations, frequencies) will be presented for primary and secondary outcome measures at each time point. All data for primary and secondary outcomes will be analysed using an intention-to-treat analysis, using multiple imputation (MI) to compensate for missing data at different assessment points. Imputation assumptions for MI will be reported and justified, and imputed data analysed as part of a sensitivity analysis. Parallel per protocol analyses will also be conducted for outcomes. Attrition analyses will be conducted at each time point to assess for differences between those who dropped out from the programme me and those who stayed. This will be based on an examination of key baseline variables (e.g. intervention arm, participant SES and wellbeing, child gender) and qualitative data outlining reasons for attrition.

Multiple regression techniques will be used to explore moderators of intervention effects (if present). Moderators will include: severity of risk and CM at baseline (measured using below and above clinical cut-off scores on the BCAPI, CTSPC, as well as frequency of CM incidences within substantiated reports); age and SES of parents and children (measured using a composite risk factor score derived from demographic data on the Profile Questionnaire); gender of child; parental mental health and problem substance use (using above or below clinical scores on the DASS, CAGE and DAST). Statistical analyses will be conducted using SPSS and Stata. We are aware of the possibility of low statistical power given that our numbers are lower than desired. Hence these analyses will be more exploratory in nature.

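### Five scored baseline measures are split at clinical cut-offs for the moderator analyses, although the planned regression could use the scores and lose less information

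*Protocol article*

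**What the plan says.** The moderator paragraph of the protocol article (Data analysis, RCT) names multiple regression as the tool and then states how each moderator is coded.

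- Severity of risk and maltreatment at baseline: "measured using below and above clinical cut-off scores on the BCAPI, CTSPC", followed by "as well as frequency of CM incidences within substantiated reports".
- Parental mental health and problem substance use: "using above or below clinical scores on the DASS, CAGE and DAST".
- Age and SES: "measured using a composite risk factor score derived from demographic data on the Profile Questionnaire".
- Child gender.

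So five instruments are cut in two. The count of substantiated incidents and the age/SES composite are not described as cut, and gender is binary by nature.

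Earlier in the same section, the outcome analysis works with scores: "Changes in continuous primary and secondary outcomes at baseline and at six-month follow-up will be compared" by ANCOVA with the baseline score as a covariate. The only outcomes that the section lists as categorical are the agency records of maltreatment and of out-of-home placement.

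On power, the moderator paragraph closes with "We are aware of the possibility of low statistical power given that our numbers are lower than desired" and calls these analyses more exploratory. The Abstract gives the size: families "will be randomised to either the 20-week ChARM programme (n = 25) or to standard care (n = 25) using a 1:1 allocation ratio".

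**The concern.** The coding is a stated choice of method, not a detail left to a later analysis plan. It spends information that the trial has already paid to collect. Within each half, a family just past the cut-off counts the same as one far past it, and two families on either side of the line count as different however close their scores are. Regression does not need this step.

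The article is also uneven. For the CTSPC outcome, the baseline CTSPC enters the ANCOVA as a score, yet as a moderator the same variable is cut. Two other moderators stay uncut. No reason is given for treating these five differently.

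At stake is the precision of most of the planned quantitative tests of which families respond differently. Interactions are hard to estimate in 50 families, so a loss of a third to a half of the information matters more here than in a large trial. If few families, or nearly all, lie above a cut-off, the estimate also rests on a handful of families in one cell of each arm.

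**Working it through.** **Plan's own figure.** There is none for the moderator analyses. The sample-size statement concerns the main effect on the primary outcomes and is not used here.

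**Inputs from the article.** 50 families, 25 per arm (Abstract). Attrition of 30% (Sample size), so 50 × 0.70 = 35 families, or 17.5 per arm. The article reports 95% CIs, so a two-sided 5% test is assumed.

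**Inputs assumed.** The share p above a cut-off is not given, so a range is shown. The score is taken as roughly normal and the moderator effect as linear. The interaction is set at 0.8 residual SD per moderator SD. That is large and does not come from the article, whose own 0.8 is a main effect.

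**1. Information kept by the split.** With c = z(1 − p) and φ the normal density, the share kept is R = φ(c)² / [p(1 − p)]. At p = 0.5, φ(0) = 0.399, so R = 0.159/0.25 = 0.637.

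| Share above cut | Kept | Lost |
|---|---|---|
| 50% | 64% | 36% |
| 40% | 62% | 38% |
| 30% | 58% | 42% |
| 20% | 49% | 51% |
| 15% | 43% | 57% |
| 10% | 34% | 66% |

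The table is symmetric: 80% above loses the same as 20% above. For a skewed (exponential) score, the loss is 35% to 52% for p between 10% and 50%.

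**2. Interaction power, normal approximation.** Power ≈ Φ(0.8·√(N·R)/2 − 1.96). With N = 50 and the score kept (R = 1): 0.8 × 7.07/2 = 2.83, and Φ(0.87) = 81%. With R = 0.637: 2.83 × 0.798 = 2.26, and Φ(0.30) = 62%. At 30/70 and 20/80 it is 57% and 51%.

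**3. Interaction power, simulation.** The approximation flatters the split, because the score's effect within each half goes into the residual. The simulated model is y = 0.5x − 0.4·arm + 0.8·arm·x + error, with error SD 1, testing the interaction with x as a score or cut.

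| N | Score | 50/50 | 30/70 | 20/80 |
|---|---|---|---|---|
| 50 | 75% | 44% | 39% | 29% |
| 35 | 57% | 33% | 28% | 22% |

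Independent runs gave cut-version values of 44–50%, 39–42% and 29–33% at N = 50, so read these figures to within a few points. With an interaction of 0.3 at N = 50, power is about 17% with the score against 11% (50/50) or 9% (20/80).

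**4. Cell sizes.** The expected number above the cut per arm is p × arm size: at 50%, 12.5 (8.8 after attrition); at 30%, 7.5 (5.3); at 20%, 5 (3.5); at 10%, 2.5 (1.8). For p = 0.2 and 25 per arm, the binomial chance of fewer than 5 is 0.42, so for at least one arm it is 1 − (1 − 0.42)² ≈ 66%.

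| Split | Fewer than 5 in an arm, N = 50 (35) | 2 or fewer in an arm, N = 50 (35) |
|---|---|---|
| 20/80 | 66% (93%) | 19% (50%) |
| 30/70 | 17% (59%) | 2% (13%) |
| 50/50 | 0.1% (4%) | below 1% (below 1%) |

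**The case against.** The strongest reply is that the article has already conceded the point that matters: power is low, the moderator work is exploratory, and the Discussion repeats the caution. No primary or secondary treatment comparison rests on it. With a smaller interaction, neither coding is informative, as the 0.3 case shows. This stands, and it limits the weight of the point. It does not make the weaker coding preferable, because the label governs what may be claimed, not how efficiently the data are used.

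A second reply is that clinical cut-offs are set in advance, are not chosen from the data, and are easy for services to read. CAGE and DAST are short screeners. If scores cluster near zero once families with unstable substance use are excluded, a linear interaction could hang on a few extreme families. This also stands: the score version is not free of risk.

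Three stronger readings are tempting, and the article does not support them:

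- A reader might infer that the split will leave near-empty cells, since families are selected as at risk and unstable substance use is excluded. Uneven splits are plausible, but no cut-off value, score distribution or share above a cut-off is given. With 30% to 50% above the cut, each arm would hold about 7 to 12 families there, or 5 to 9 after attrition.
- A reader might infer that every scored moderator is dichotomised. The count of substantiated incidents and the age/SES composite are not.
- A reader might take these five tests as the trial's sole evidence on which families benefit. The uncut moderators, child gender and the possible sensitivity analysis of cost-effectiveness by baseline severity also bear on that question.

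**Conclusion.** The point holds as a minor, specific inefficiency in a stated method. Splitting the BCAPI, CTSPC, DASS, CAGE and DAST at clinical cut-offs loses about 36% to 51% of the moderator information if 20% to 80% of families exceed the cut, and more outside that range. Under the assumed interaction of 0.8, that takes power at N = 50 from about 75% to between about 44% and 29%.

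The loss figures rest on a roughly normal score and a linear moderator effect, and fit short screeners least well. The power figures rest also on the assumed interaction, an error SD of 1 and a two-sided 5% test. Sparse cells are a possibility that depends on unstated shares. A share of about 10% to 15% or fewer above the cut (or 85% to 90% or more) would bring them, and the information loss would then be about 57% to 66% or more rather than a third to a half.

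The analyses stay exploratory and low-powered under either coding, and no primary conclusion changes.

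**What to change.** In the moderator paragraph, replace the above/below coding of the five instruments with centred baseline scores. Fit an arm-by-score interaction in the planned regression, with the main effects of arm and score, and report the interaction with its 95% CI. Use the clinical cut-offs only to display predicted treatment effects at meaningful score values.

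Add a check of linearity and of influential points, above all for CAGE and DAST. For these two, the cut-off version can be kept as a sensitivity analysis, with the number of families per arm on each side of the cut reported.

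The cost is a change of analysis wording and a short diagnostic step. No new data are needed, and the Trial status section says that data are still being collected, so the change can be dated before the outcome analysis.

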### Sample size

Due to major restructuring of services and staff within the Tusla Child and Family Agency in 2014–2016, our key collaborating site had to withdraw from the research. Thus, our sample size will be smaller (n = 50) than that advised by our sample size calculation that indicated that, factoring in 30 per cent attrition, we would need to recruit 150 families to detect a 0.8 effect size on our primary outcome measures. Given the reduced sample size, the results of this RCT should be interpreted with some caution.

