Interviews will be conducted in the participants’ home/place of work or a local health care centre. Participants can elect whether to participate in an individual interview or a focus group. Written informed consent will be requested. Interviews will be audio-recorded (with participants’ consent) and will last no more than one hour with parents and service providers, and no more than 30 minutes with children. The parent of the child will be approached to seek their consent for their child to participate in the study and we will also seek the child’s written and verbal assent. To reduce participant burden, interviews with parents and children will be conducted at a different time from the administration of the measures for the impact evaluation.

***Costs analyses.*** In order to estimate the costs per family of delivering the ChARM programme, comprehensive cost diaries will be completed by sites (practitioners and managers) during and following the implementation process. Costs will be collected on: costs of training and supervision, staff time and materials involved in preparation, recruitment of families, intervention delivery, managerial overheads, referrals, and so forth. Parents (n = 50) will also complete a Services Utilization Questionnaire (SUQ) at baseline and 6-month follow up in order to record all health, educational and social services used by the family in the previous six months. The SUQ is based on an adaptation of the Client Service Receipt Interview (
Beecham & Knapp, 1992).

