***Economic evaluation.*** A societal perspective (public sector perspective and individual costs incurred by participants in attending the intervention) will be taken in the economic analysis. The CEA will be calculated through a three-step process. Firstly, the costs diaries will estimate the cost per family of delivering the programme. Unit costs of health and social care services used by families (e.g. GP, nursing, hospital visits) will be obtained from official government documentation, official government pay scales, the Casemix/HIPE unit of the Health Service Executive and any other relevant sources and/or agencies. Thirdly, a CEA will calculate an incremental cost-effectiveness ratio (ICER) to give the cost of obtaining a one-unit decrease on the two primary outcome measures (CTSPC-SF and SDQ) when comparing the ChARM programme to usual services at six-month follow up.

The ICER will use a 1000 replication bootstrap to provide a 95% CI accompanied by appropriate sensitivity analyses. Such sensitivity analyses may include how the ICER may vary according to the severity of the presenting problem at baseline or, for example, excluding non-recurrent costs (e.g. training, materials). The ICER accommodates sampling (or stochastic) uncertainty and varying levels of willingness to pay for reductions in the primary outcomes of interest.

A CBA will also be conducted to investigate the down-stream impact of the intervention on later costs, such as generating savings in relation to reduction in child welfare services, foster and residential placements, health and mental health service utilization, crime, education and unemployment. To conduct the CBA, the results of the CEA will be combined with estimates of the effects of CM on key outcomes in adult life. The effects of CM on adult outcomes can be assessed using secondary data sources and a monetary value will be assigned to the associated gains/losses of programme me delivery. The CBA will calculate an ‘internal rate of return’ to assess the desirability of investment in the programme. The ‘internal rate of return’ refers to the discount rate at which the value of the stream of future benefits exactly equals the initial cost of the programme, yielding a net present value equal to zero.

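### The cost-effectiveness analysis as described gives no role to the baseline service costs the trial collects, or to site, so the incremental cost may be less precise than the data allow

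*Protocol article*

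**What the plan says.** Under Measures, Costs analyses, the protocol article says of all 50 parents that they "will also complete a Services Utilization Questionnaire (SUQ) at baseline and 6-month follow up". Each completion covers the family's service use over the preceding half-year, across health, education and social care. Under Randomisation and blinding, allocation follows the baseline assessments and is stratified by site. The first questionnaire is therefore a pre-randomisation measurement of the service-cost outcome.

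Under Data analysis, Economic evaluation, programme cost comes from cost diaries and service use is valued with unit costs. Then "a CEA will calculate an incremental cost-effectiveness ratio (ICER) to give the cost of obtaining a one-unit decrease on the two primary outcome measures", for ChARM against usual services at six months. On uncertainty: "The ICER will use a 1000 replication bootstrap to provide a 95% CI accompanied by appropriate sensitivity analyses". The only baseline item named there is an optional sensitivity analysis of "how the ICER may vary according to the severity of the presenting problem at baseline", which concerns clinical severity and not prior cost.

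Under Data analysis, RCT, continuous primary and secondary outcomes are compared by ANCOVA "controlling for intervention status, site, baseline score" and other baseline differences found. Costs are not among those outcomes.

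**The concern.** The article names baseline and site adjustment for the clinical effect but no adjustment for the cost, although the covariate for the cost model is collected from every family. Families who used many services before entry may well continue to do so. A cost comparison that ignores prior use then leaves explainable variation in the estimate, and lets a chance difference between two small arms move it.

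Cost-effectiveness is one of the study's stated objectives, and the cost-benefit analysis is built on its results, so avoidable noise in the incremental cost can carry into both.

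**Working it through.** The article gives no cost SD, cost correlation, incremental cost or ICER, so there is no figure of its own to reproduce. The check is done in units of the cost SD.

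**Inputs**
- Arm size: 25 per arm; the Abstract says families "will be randomised to either the 20-week ChARM programme (n = 25) or to standard care (n = 25) using a 1:1 allocation ratio".
- Attrition: 30%, from Sample size, which gives 25 × 0.7 = 17.5 per arm.
- Correlation rho between baseline and six-month cost within arm: not given. Assumed values are 0.3, 0.5 and 0.7.

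**1. Size of a chance baseline imbalance.** SE = sqrt(2/n).
- n = 25: sqrt(2/25) = 0.283 SD. P(|imbalance| > 0.25 SD) = 2 × (1 − Φ(0.25/0.283)) = 38%; for > 0.5 SD it is 8%.
- n = 17.5: sqrt(2/17.5) = 0.338 SD. The same probabilities are 46% and 14%.

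These figures hold for any baseline variable at these arm sizes, and the cut-offs are only illustrative.

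**2. How much carries over.** An imbalance of δ SD moves an unadjusted cost difference by rho × δ on average. For δ = 0.25 SD, that is 0.075, 0.125 or 0.175 SD at rho = 0.3, 0.5 or 0.7.

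**3. Gain from adjustment.** Unadjusted SE = sqrt(2/n); adjusted SE = sqrt(2/n) × sqrt(1 − rho²). The relative reduction is 1 − sqrt(1 − rho²), and the equivalent sample size is multiplied by 1/(1 − rho²).

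| Assumed rho | SE unadjusted, n = 25 | SE adjusted, n = 25 | SE adjusted, n = 17.5 (unadjusted 0.338) | Reduction in SE | Equivalent extra families |
|---|---|---|---|---|---|
| 0.3 | 0.283 | 0.270 | 0.322 | 5% | 10% |
| 0.5 | 0.283 | 0.245 | 0.293 | 13% | 33% |
| 0.7 | 0.283 | 0.202 | 0.241 | 29% | 96% |

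Estimating the slope costs a little. Multiplying the adjusted SE by sqrt(1 + 1/(2n − 4)) = sqrt(47/46) = 1.011 gives 0.273, 0.248 and 0.204 at n = 25. On that approximation, adjustment for baseline cost breaks even at rho² = 1/47, or rho of about 0.15.

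**4. Skewed costs.** The formulas above do not depend on the shape of the cost distribution in any detail, so they were checked in 20,000 simulated trials with lognormal costs and 25 per arm. The unadjusted difference averaged 0.002 SD, that is, no bias. Its SD was 0.282 against 0.253 after adjustment when the raw cost correlation was 0.42, and 0.286 against 0.213 when it was 0.63.

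**The case against.** The strongest reply is that the article is silent on how the cost difference is estimated. A comparison at six months names the endpoint and not the estimator: the clinical ANCOVA also compares arms at six months, and it adjusts for baseline. Covariates for a cost model may sit in a fuller economic plan that is not shown. This stands. A reader might infer that the plan specifies an unadjusted cost difference; the text does not support that.

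Three other strong readings also fail:
- **Bias.** Randomisation keeps an unadjusted difference unbiased, and a bootstrap of families within arm reflects its variance. The interval would be wider than necessary, not invalid.
- **Imbalance passing in full into the cost.** Only the fraction rho does, and rho is unknown.
- **An ICER denominator that disagrees with the reported clinical effect.** That would need raw arm means, which the article nowhere mentions. The natural reading is that the ANCOVA effect is used.

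The gain may also fall short of the table. Total cost in the ChARM arm includes programme cost, the number of home visits varies by family, and caseworkers link families to further services during follow-up. Each could weaken prediction from baseline cost. Stratified randomisation already limits imbalance by site. Finally, the article asks for caution given its size and calls the trial exploratory.

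What remains is that the economic method is described down to the number of bootstrap replicates. An analyst who follows those steps has no instruction to use the baseline questionnaire or site.

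**Conclusion.** The point holds as an improvement in efficiency, not as an error, contradiction or source of bias. The cost-effectiveness analysis as described assigns no role to baseline service cost or to site. If it is carried out that way, the incremental cost is less precise than the collected data allow, and chance differences in prior service use can shift the estimate in this one trial.

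The size depends on a correlation that the article does not give: from a slight gain at 0.3 to a substantial one at 0.7. These are likely upper figures to the extent that programme cost adds variation unrelated to prior service use.

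**What to change.** In Data analysis, Economic evaluation, state that:
1. the incremental cost is estimated by regression of six-month cost on arm, site and baseline six-month service cost from the questionnaire;
2. the incremental effect on each primary outcome is taken from the ANCOVA already described for the trial;
3. each of the 1000 bootstrap replicates resamples families with their cost and effect kept paired, within arm and site, and refits both models.

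If a fuller economic plan already says this, a one-line reference to it is enough. The cost is a few sentences and a few lines of code, with no new data, visits or burden on families. Data were still being collected when the article was written (Trial status). Settling this before the cost data are analysed also avoids choosing the estimator after seeing the costs.
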